### Sample size

As this is a pilot feasibility study, a formal sample size calculation will not be performed. We will aim to have 12 participants minimum per group as a rule of thumb as recommended in the literature [53].

### Statistical analysis

To assess the primary feasibility outcome measures, data pertaining to participant recruitment, withdrawal and completion of intervention will be analysed as percentages. Compliance will also be calculated based upon percentage completion of rehabilitation sessions as collated in Salaso or in the training diaries. An intention to treat analysis will be performed on the clinical outcome measures. Using SPSS software version 24 means and standard deviations (or frequencies and proportions for categorical data), mean or median differences and 95% confidence intervals for clinical outcome measures will be calculated. Although this pilot feasibility study is not powered to detect an effect of treatment, analysis of co-variance (ANCOVA) adjusting for baseline values will be used on the primary clinical outcome measure.

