### Secondary objectives:

Explore trends in treatment effects, comparing mean pre-post differences in clinical outcome measures across groups to minimum clinically important differences where possibleExplore the relationship with fear of movement, central sensitisation and AOTConduct a power calculation to determine the numbers needed for a future large-scale randomised controlled trial

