### Primary clinical outcome measure

#### Disability

The primary clinical outcome measure will be the Victorian Institution Symptom Assessment-Achilles Questionnaire (VISA-A); consists of 8 questions assessing pain, function and ability to participate is activity. Scores range from 0 to 100, with the higher scores representing a lower clinical severity [38]. The VISA-A has been validated in persons with AT and has robust psychometric properties with excellent reliability reported. As both athletic and non-athletic participants will be recruited, the eight question will use the word ‘physical activity’ to ensure inclusivity. This adjustment has been used previously in research [39].

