#### Exercise intervention

Both the AOT and control groups will perform the same physical exercises. The Alfredson eccentric heel drop protocol [6] will be used for the exercise training component (Fig. 3). Post baseline measurements during the initial online assessment, participants will be briefed as to how to correctly perform the two exercises to ensure correct technique throughout the clinical trial. This programme consists of two Achilles eccentric loading exercises to be performed twice a day, for 3 sets of 15 repetitions. Both exercises require the participant to stand on the edge of a step with body-weight on the forefoot. The participant rises on the non-injured leg into plantar flexion and lowers eccentrically on the injured leg, so that the heel lowers below the level of the step. The un-injured leg is then used again to return to the starting position of plantarflexion. The hands are placed on the wall or a railing for balance support. The first exercise is performed with the knee straight, whilst the second exercise is performed with the knee bent (Fig. 3).

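### Baseline-adjusted ANCOVA is named for VISA-A only, and the trend objective can be read as setting within-arm changes against MCIDs (low severity, free to fix)

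*Protocol article*

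**What the plan says.** In the protocol article, the Statistical analysis section makes two statements about clinical outcomes. For all of them, "mean or median differences and 95% confidence intervals for clinical outcome measures will be calculated". For one of them, "analysis of co-variance (ANCOVA) adjusting for baseline values will be used on the primary clinical outcome measure". The Disability section identifies that one: "The primary clinical outcome measure will be the Victorian Institution Symptom Assessment-Achilles Questionnaire (VISA-A").

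The abstract's Methods paragraph places outcome assessments at baseline, week 6 and week 12, and the Baseline assessment section lists the clinical outcome measures. A baseline value is therefore collected for the secondary scores as well. The exceptions are Patient Global Impression of Change, which has none by construction, and satisfaction with treatment, which cannot be rated before treatment.

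The Secondary objectives section describes how trends in treatment effect will be explored: "comparing mean pre-post differences in clinical outcome measures across groups to minimum clinically important differences", where possible. The Exercise intervention section says: "Both the AOT and control groups will perform the same physical exercises". On size, the Sample size section says "a formal sample size calculation will not be performed" and "We will aim to have 12 participants minimum per group as a rule of thumb as recommended in the literature".

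**The concern.** There are two linked points.

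First, the plan names baseline adjustment for one score and stops there, although the same covariate is collected for the others. With about 12 per arm, randomisation will often leave a visible baseline difference on a given score. An estimate that ignores it carries part of it into the apparent treatment effect, and is usually less precise than it could be.

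Second, the trend objective does not say which quantity is compared with the MCID. If it is each arm's own pre-post change, the result mixes any AOT effect with the exercise effect, natural recovery and regression to the mean. Both arms could pass an MCID when AOT adds nothing. The objective covers clinical outcomes in general, so VISA-A is included and would have two summaries that need not agree: the ANCOVA estimate and the pre-post comparison.

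At stake is how the secondary results are read. The Discussion section says the results will help decide whether a larger trial is warranted.

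**Working it through.** **Inputs.** From the Sample size section, n = 12 per arm. This is a rule of thumb with no alpha, power, effect size or SD behind it, so there is no stated calculation to reproduce. The article gives no pre-post correlation r, no MCID value and no expected improvement. These are assumptions, shown as ranges. Everything is in SD units with equal SD before and after.

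**1. Chance imbalance at baseline.** The SE of the between-arm baseline difference is √(2/12) = 0.408. The probability of an imbalance above 0.5 SD in either direction is P(|Z| > 0.5/0.408) = P(|Z| > 1.22) = 0.22 for any one outcome.

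**2. What an imbalance D does.** It shifts a final-score difference by r·D and a change-score difference by −(1 − r)·D. The ANCOVA estimate is not shifted.

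**3. Precision.** The SEs are:
- final score: √(2/n)
- change score: √(2/n)·√(2(1 − r))
- ANCOVA: √(2/n)·√(1 − r²)·√(1 + 1/(2n − 4))

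The last factor is the small-sample penalty for estimating the slope. Its square is 1 + 1/20 = 1.05. The variance ratio of ANCOVA is therefore 1.05(1 − r²) against final scores and 1.05(1 + r)/2 against change scores.

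| r (assumed) | SE final | SE change | SE ANCOVA | Variance ratio vs final | Variance ratio vs change | Shift in final score at D = 0.5 | Shift in change score at D = 0.5 |
|---|---|---|---|---|---|---|---|
| 0.3 | 0.408 | 0.483 | 0.399 | 0.96 | 0.68 | +0.15 | −0.35 |
| 0.5 | 0.408 | 0.408 | 0.362 | 0.79 | 0.79 | +0.25 | −0.25 |
| 0.7 | 0.408 | 0.316 | 0.299 | 0.54 | 0.89 | +0.35 | −0.15 |
| 0.8 | 0.408 | 0.258 | 0.251 | 0.38 | 0.95 | +0.40 | −0.10 |

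A simulation of 20,000 trials at r = 0.5 gave SEs of 0.409, 0.408 and 0.362, with all three mean estimates close to zero when there was no effect.

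**4. How much of the error is imbalance.** Its share of the sampling variance is r² for final scores and (1 − r)/2 for change scores. For r = 0.3, 0.5, 0.7 and 0.8 this is 9%, 25%, 49% and 64% (final) and 35%, 25%, 15% and 10% (change).

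**5. The shared exercise effect.** Assume no AOT effect, r = 0.5 and the same true improvement m in both arms. The SE of one arm's mean change is √(2(1 − 0.5)/12) = 0.289. The SE of the between-arm difference in change is 0.408.

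| m (assumed) | MCID (assumed) | P(AOT arm's own change reaches the MCID) | P(between-arm difference reaches it in AOT's favour) |
|---|---|---|---|
| 0.5 | 0.5 | 0.50 | 0.11 |
| 1.0 | 0.5 | 0.96 | 0.11 |
| 1.5 | 0.5 | 1.00 | 0.11 |
| 0.5 | 0.8 | 0.15 | 0.025 |
| 1.0 | 0.8 | 0.76 | 0.025 |
| 1.5 | 0.8 | 0.99 | 0.025 |

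The within-arm comparison depends on m. The between-arm comparison does not, because m cancels.

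**The case against.** Several stronger readings are tempting, and the article does not support them.

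- A reader might infer that the other outcomes will get raw, unadjusted differences. The text does not say so. It leaves open whether the differences are within or between arms, on final or change scores, adjusted or not. A fuller plan may settle this, and leaving such detail to it is not a fault. What stands is that the article names a scope for the adjustment and that scope is VISA-A.
- A reader might infer that the shared exercise effect contaminates the trend comparison. That holds only if each arm's change is set against the MCID. The objective refers to a comparison across groups and to treatment effects. Read as the between-arm difference in change, the shared effect cancels. The fault is that the wording permits both readings.
- A reader might infer that chance imbalance will drive the trends. Randomised unadjusted estimates are unbiased on average. Imbalance exceeds half the sampling variance only for final scores with r above about 0.71 (r² > 0.5). Ordinary sampling error usually dominates: at r = 0.5, ANCOVA narrows the 95% CI half-width only from about 0.85 to 0.75 SD.
- A reader might infer that these estimates decide whether the main trial goes ahead. The Progression criteria section uses retention and enrolment only, and the Statistical analysis section says that "this pilot feasibility study is not powered to detect an effect of treatment".

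It is also fair to say that linear ANCOVA does not suit every scale. The Widespread Pain Index is a 0 to 19 count, and the EuroQol is described only as five five-level dimensions. The plan's option of median differences should be kept for such scales. Twelve per arm is a minimum, so imbalance shrinks somewhat if more are recruited.

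**Conclusion.** The point holds as a low-severity improvement. Baseline-adjusted ANCOVA is specified for VISA-A only, although the other clinical scores also have a baseline, and the trend objective is worded so that within-arm changes may be compared with MCIDs.

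The 22% chance of an imbalance above 0.5 SD rests only on 12 per arm and approximate normality. The shifts and precision gains also rest on assumed correlations of 0.3 to 0.8 and equal SDs. Over that range ANCOVA is the most precise of the three estimates even after the penalty, though by little against final scores at r = 0.3 and against change scores at r = 0.8. The penalty would outweigh the gain over final scores only where 1.05(1 − r²) > 1, that is r below about 0.22, and over change scores only where 1.05(1 + r)/2 > 1, that is r above about 0.90. The MCID illustration rests on assumed values of m, MCID and r, and applies only to the within-arm reading.

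The estimates stay wide whichever analysis is used. These are exploratory secondary outcomes, and no progression criterion depends on them.

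**What to change.** In the Statistical analysis section:
- Extend the VISA-A model (group plus baseline value) to the other approximately continuous outcomes that have a baseline.
- Keep the median-based option for skewed or ordinal scales.
- State that Patient Global Impression of Change and satisfaction are not baseline-adjusted.
- Report the adjusted between-group difference with its 95% CI.

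In the Secondary objectives section:
- Reword the trend objective so that any MCID comparison meant to inform on a treatment effect, VISA-A included, uses that between-group difference and its CI.
- Label within-arm pre-post changes as descriptive.

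The cost is wording and one degree of freedom per model. No new data, visits or participants are needed.

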### Progression criteria

The following criteria must be met in order to consider progression to a main RCT:A retention rate of ≥ 80% of recruited participantsA minimum of ≥ 80% of eligible participants enrol in the study

## Discussion

The aim of this study is to evaluate the feasibility of a future larger scale randomised controlled trial examining the effectiveness of AOT combined with Achilles tendon eccentric exercises in the rehabilitation of mid-portion AT. The results from this pilot feasibility study will provide critical data to guide and inform whether a larger-scale randomised controlled trial is warranted. This protocol represents an integrated treatment approach specifically designed to address the possible central and peripheral changes that can occur during mid-portion AT. Whilst potentially providing the needed solution to current rehabilitation programmes to successfully rehabilitate mid-portion AT, this protocol is representative of the MRC guidance for developing and evaluating complex interventions [34]. It is designed to be delivered remotely by physiotherapists and thus allows access to care for patients whom otherwise may not be able to receive such care due to time or transport limitations, along with the national social limitations implemented due to the pandemic.

### Trial status

Recruitment is scheduled to begin in January 2021.

## Abbreviations

AT: Achilles Tendinopathy
AOT: Action observation therapy
VISA-A: Victorian Institution Symptom Assessment-Achilles Questionnaire
ICON: International Scientific Tendinopathy Symposium consensus
NPRS: Numeric Pain Rating Score
LEFS: Lower Extremity Functional Scale
TSK: Tampa Scale for Kinesiophobia
WPI: Widespread Pain Index
